## **b. Inclusion and Exclusion Criteria**

For Objectives 1-5 and Objective 8, we will enroll a specific cohort of patients. These will be numbered in accordance with the objective number for Objectives 1-5; for Objective 8, the cohort will be called the “TBHD cohort”, in reference to tuberculosis, hypertension, and diabetes. This TBHD cohort will be made up of patients who have been screened for TBHD (50%) and patients who are newly diagnosed with TB, hypertension or diabetes (50%). For all cohorts, inclusion and exclusion criteria are as shown below. For Objectives 1-5, these criteria follow the December 2014 national guidelines for HIV care and ART[10] and November 2015 National Adherence Guidelines for Chronic Disease (HIV, TB and NCDs) [11].

*Cohorts 1-5 and TBHD cohort inclusion criteria*

- ≥ 18 years old
- Meet the inclusion criteria for one or more of Cohorts 1-8

*Cohorts 1-5 and TBHD cohort exclusion criteria*

- Not resident in the facility’s catchment area
- Recorded intention to transfer care to a different facility within 12 months
- Pregnant and eligible for PMTCT

*Objective 1/Cohort 1 inclusion criteria (Patients newly eligible for ART—fast track treatment initiation)*

- Determined to be eligible to start ART under prevailing national guidelines (CD4 count < 500, WHO Stage 3 or 4 condition, TB, cryptococcal meningitis)

*Objectives 2 and 3/Cohorts 2 and 3 inclusion criteria (Patients stable on ART—adherence clubs or decentralized medication delivery)*

- On same ART treatment regimen for at least 12 months
- Most recent viral load taken in past 6 months
- Two consecutive viral loads undetectable (<400 copies/ml^3^)

*Objective 4/Cohort 4 inclusion criteria (Patients on ART with poor adherence—enhanced adherence counseling)*

- On first line ART for at least 6 months
- Poor adherence as indicated by an elevated viral load (>400 copies/ml^3^)

*Objective 5/Cohort 5 inclusion criteria (Patients lost from ART programs—early patient tracing)*

- Initiated ART
- Fail to return for a scheduled appointment within 5 to 90 days from their appointment date

*Objective 8/TBHD cohort inclusion criteria (Tuberculosis, hypertension, and diabetes patients)*

- Screened for or diagnosed with for TB or hypertension within the last month, or diabetes within last 6 months

*Objective 8/TBHD cohort exclusion criteria (Tuberculosis, hypertension, and diabetes patients)*

- Patients with existing TB, hypertension (diagnosed more than 1 month ago) or diabetes (diagnosed more than 6 months ago)

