# TUBERCULOSIS, HYPERTENSION, AND DIABETES (OBJECTIVE 8)

Under Objective 8 we will collect baseline data to help tailor the adherence interventions to other chronic conditions in the future. This objective will focus on drug-susceptible tuberculosis, adult Type 2 diabetes mellitus, and hypertension. Routinely collected data will be used to estimate proportions of patients diagnosed with each condition, treatment uptake, and treatment retention at the same study sites in the cluster randomized trial.

The Adherence Guidelines address tuberculosis and common non-communicable diseases, like hypertension and diabetes, as well as HIV. Unlike for HIV, where much is known about the care cascade and where the “leaks” in the cascade have been identified and estimated, little is known about the care cascade for TB and even less for diabetes and hypertension. A better evidence base about current retention in care and treatment outcomes is needed to assess the magnitude of the problem and define areas most in need of targeting for adherence support before the minimum package of adherence interventions is offered to patients in these populations.

To generate this evidence, we will use routinely collected data from the same clinics at which the HIV interventions will be evaluated. From existing medical records, we will estimate the proportions of patients presenting at the clinics who are screened for TB, hypertension, and/or diabetes and those retained in care at various steps along the diagnostic and treatment cascade, stratified where data allow by HIV status, sex, age, and/or other variables. Details on specific outcomes to be estimated, sample size, and data sources are provided in later sections of this protocol.

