**Table 2. Data required for the evaluation**

| **Objective** | **Data that must be fully captured by routine data collection systems and procedures** |
| --- | --- |
| Fast track ART initiation counseling (Objective 1) | Scheduled and actual visit date information, CD4 counts and dates when results are received, date at which ART eligibility is determined, date of first ARV dispensing, viral loads. |
| Enhanced adherence counseling (Objective 2) | Scheduled and actual visit information, date of eligibility for enhanced adherence counseling, dates of delivery of counseling, viral loads. |
| Adherence clubs (Objective 3) | Club membership, scheduled and actual visit/club participation information, date of eligibility, dates of all medication pick ups, viral loads. |
| Decentralized medication delivery (Objective 4) | Scheduled and actual visit information, date of eligibility, dates of all medication pick ups, viral loads. |
| Early tracing (Objective 5) | Scheduled and actual visit information, date of eligibility, numbers and types of tracing attempts made, results of tracing, viral loads. |
| Overall impact (Objective 6) | Aggregate figures of total numbers of patients presenting and eligible for each intervention (aggregate at clinic level).*  (*Note: as these data do not pertain to individual human subjects, they are not included in the list of fields below.) |
| Cost estimates of interventions (Objective 7) | Unit costs of all resources utilized to implement the interventions.* (*Note: as these data do not pertain to individual human subjects, they are not included in the list of fields below.) |
| TB, diabetes and hypertension (Objective 8) | Records for all patients recently screened for these conditions, all laboratory tests and clinical investigations done relating to these conditions (including blood pressure, HbA1c test and TB test results), scheduled and actual visit information, dates of eligibility, dates of all medication pickups, and outcome data. |

The specific data fields available and required for each cohort will vary slightly (e.g. viral loads will not be available for patients newly initiating treatment under Objective 1). In general, however, we will collect a common set of variables for all patients enrolled Cohorts 1-5, and a different set of variables for patients enrolled in Cohort 8, as listed below.

*Objectives 1-6, all cohorts:*

- Electronic medical record system number (e.g. Tier.Net record number)*

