## **c. Duration of Follow Up**

Study enrollment will begin on the date of determination of eligibility for an intervention (Cohorts 1-5) during the enrolment period. Enrolment for cohort 8 will begin if date of eligibility (screening or diagnosis date) was in the last month for TB and Hypertension patients and within the last 6 months for Diabetes patients.

Passive follow up through medical record review will continue for a minimum of 14 months after the date of enrollment (two additional months beyond twelve months to allow one year outcomes to occur). This will allow all subjects sufficient follow up time to complete each of the primary outcomes designated. Patients enrolled early in the study will have up to 20 months of passive follow-up, assuming a six-month enrollment period. Medical records will be checked for each patient after each clinic visit.

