| Overall impact (Objective 6) | Proportion of population in need at each clinic who achieve the short term primary outcomes defined above. | Proportion of population in need at each clinic who achieve the long term primary outcomes defined above. |
| Cost  (Objective 7) | Average cost per patient receiving an adherence intervention | Average cost per primary outcome achieved; average cost per 1000 patients receiving the observed mix of interventions |
| TB, hypertension, and diabetes (Objective 8) | For each condition, proportion of patients eligible for treatment who have 80% visit compliance in the first three months after diagnosis (S) and who achieve disease control at the six-month visit after diagnosis (L) as indicated in “Primary Care 101,” the NDOH’s guide for primary health clinic services[15]. The six-month visit will be represented by the visit closest to six months within the window of 5-8 months after diagnosis. The disease control indicators to be measured, with page references for Primary Care 101, are:  TB: cured or treatment completed indicated as the patient’s status at 6 months (page 57)  Hypertension: blood pressure controlled at 6-month visit, with control defined as < 140/90 (or 120/70–140/80 if diabetes, or <130/80 if CVD, heart failure or kidney disease) (page 74)  Diabetes: random glucose < 8 or HbA1c ≤ 7% at 6 month visit (page 71) | Among patients screened, prevalence of pre-diabetes elevated blood sugar (defined by Primary Care 101 as random glucose between 7.8 and 11) and pre-hypertension elevated blood pressure that require monitoring  Proportion of patients diagnosed with pre-diabetes or pre-hypertension who a) progress to diabetes and hypertension; or b) remain in care and receive appropriate monitoring for their condition over 12 months  Prevalence of diabetes, hypertension and TB among patients screened  Proportion of diagnosed patients initiated on appropriate treatment  Proportion of patients on treatment retained in care at 12 months. Loss to follow up will be defined as being 30 days late for a scheduled appointment.  Demographic and clinical characteristics of patients who do and do not achieve primary outcomes. |

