| Objective 7—Cost | 0 patients | No additional subjects will be enrolled for the cost estimates, which will rely on data from Cohorts 1-5. |
| Objective 8—TB, hypertension, and diabetes | 4800 patients | Because Objective 8 is descriptive in nature, no specific sample size will be targeted. We will instead include up to the first 100 patients per site who are eligible for screening and 100 patients who are recently diagnosed and treated for TB, hypertension and/or diabetes, for a total of 4800. (We note that some patients eligible for the TBHD cohort will also be eligible for Cohorts 1-5, due to co-morbidities with HIV. These patients will be co-enrolled in both cohorts.) |

Total enrollment will thus be 2,880 in cohorts 1-5 and 4,800 in the TBHD cohort, for a total sample size of 6,680.

Due to the size criterion for study site selection, with all clinics included in the evaluation having at least 1,000 current ART patients, we anticipate being able to enroll the target sample sizes for all cohorts during a 6-month enrollment period. Enrollment for Cohorts 4 and 5 and 8 may take longer than this depending on baseline rates of viral suppression and visit compliance at the selected clinics and number of newly screened and diagnosed TBHD patients.

We will monitor the data for Cohorts 1-5 closely and amend the protocol to increase the sample size for these cohorts if needed to ensure adequate analytic power.

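### The screening half of the TBHD cohort is defined in two ways, and under the section 8b rule it cannot supply the proportion of presenting patients who are screened

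*Protocol*

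**What the plan says.** Five places in the protocol bear on who enters the first half of the TBHD cohort.

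- **Section 8b, cohort description:** "This TBHD cohort will be made up of patients who have been screened for TBHD (50" per cent; the other half is newly diagnosed patients.
- **Section 8b, inclusion criterion:** "Screened for or diagnosed with for TB or hypertension within the last month, or diabetes within last 6 months".
- **Section 9c, enrolment date:** patients enter "if date of eligibility (screening or diagnosis date) was in the last month for TB and Hypertension patients", with a six-month window for diabetes.
- **Section 9b, Table 2, Objective 8 row:** the data needed begin with "Records for all patients recently screened for these conditions".
- **Section 10b, Table 4, Objective 8 row:** "We will instead include up to the first 100 patients per site who are eligible for screening and 100 patients who are recently diagnosed".

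Two places say what is to be estimated about patients presenting at the clinics. Section 7 states that "we will estimate the proportions of patients presenting at the clinics who are screened for TB, hypertension, and/or diabetes". The first research question under Objective 8 in section 3c asks for the prevalence of previously and newly diagnosed disease among patients presenting for care. Table 3 is narrower. It lists "Prevalence of diabetes, hypertension and TB among patients screened" as a secondary outcome and does not list the proportion screened.

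**The concern.** The first four places admit only patients who have been screened or diagnosed. Table 4 admits patients who are due for screening, whether or not it was done. These are different populations, and the choice decides whether the first step of the care cascade can be observed.

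Section 7 justifies Objective 8 by the lack of knowledge about where patients drop out of care for these three conditions. A sample selected on having been screened contains nobody who was missed at screening. The loss at that step is invisible in it, and so is the presenting population that the section 3c prevalence question refers to. An analysis plan written later could not recover patients whom the enrolment rule left out.

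**Working it through.** **Step 1. Reproduce the planned size.** Inputs: 24 clinics (section 8a); up to 100 patients in each half per clinic (Table 4).

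24 × (100 + 100) = 4,800, as Table 4 states. The first half is 24 × 100 = 2,400, and 2,400 / 4,800 = 50%, as section 8b states. The counts agree under either wording, so they do not settle which rule applies.

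**Step 2. Compare the rules for a patient who presents, is due for screening and is not screened.**

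| Place | Can this patient enter? |
| --- | --- |
| 8b, cohort description | No |
| 8b, inclusion criterion | No, neither screened nor diagnosed |
| 9c, enrolment date | No, there is no screening or diagnosis date |
| Table 2 | No, records are of screened patients |
| Table 4 | Yes |

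Table 4 stands alone, and the protocol does not define eligibility for screening.

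**Step 3. What each rule allows.** Let c be the true proportion of eligible presenting patients who are screened for at least one of the conditions.

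- Section 8b rule: everyone in the first half is screened by selection, so 2,400 / 2,400 carries no information about c. A patient screened for TB may not have been screened for diabetes, so condition-specific fractions could be below one. They would still omit everyone screened for nothing.
- Table 4 rule: the expected number screened is 2,400 × c, and c can be estimated.

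**Step 4. Look for another denominator.** Section 7 refers to existing medical records in general. Section 9a allows linkage to the PHC Tick Register as needed to complete the data set. The clinic-level aggregates in section 9a are for Objective 6 and count patients eligible for the adherence interventions. None of these defines a count of presenting patients for Objective 8.

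**Step 5. What the Table 4 rule would cost in precision.** The protocol gives no value for c, so the values below are assumptions. The 95% half-width for coverage is 1.96 × √(c(1 − c)/2,400). Intervals for prevalence among screened patients widen by 1/√c relative to 2,400 screened. Clustering by clinic is ignored.

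| Assumed c | Screened of 2,400 | Half-width for coverage (points) | Widening for prevalence |
| --- | --- | --- | --- |
| 20% | 480 | 1.6 | 2.24 |
| 40% | 960 | 2.0 | 1.58 |
| 60% | 1,440 | 2.0 | 1.29 |
| 80% | 1,920 | 1.6 | 1.12 |
| 95% | 2,280 | 0.9 | 1.03 |

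**The case against.** The strongest reply is that the protocol largely settles the rule. The eligibility section, the enrolment-date rule, Table 2 and the Table 3 denominators all speak of screened patients, and Table 4 is one phrase in a sample-size rationale. This is a good argument about which reading was probably intended. It does not supply the denominator for section 7.

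A second reply is that the proportion screened is peripheral. It is not in Table 3, and no research question in section 3c asks for it directly. The primary outcomes of Objective 8 concern patients eligible for treatment and run from diagnosis, and the screening-based outcomes are conditional on screening. All of that stands, and it limits the weight of the point. Still, section 7 makes the promise and refers to later sections for details, where it is not taken up. The section 3c prevalence question also refers to presenting patients.

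A reader might infer that the study would report 100% screening coverage and be wrong by tens of percentage points. The documents do not support that. No section plans to compute coverage inside the TBHD cohort; section 7 takes presenting patients as its base and existing records as its source. A reader might also infer that clinics would apply different rules. Section 9a does adapt procedures by site, but nothing leaves the choice of cohort rule to a clinic.

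**Conclusion.** The protocol contradicts itself on who fills 2,400 of the 4,800 TBHD places. Under the section 8b rule, the proportion of presenting patients who are screened is not estimable from the cohort, and neither the denominator for that proportion nor the one for prevalence among presenting patients is specified anywhere else. This is a missing quantity, not a biased figure. No size of error can be stated, because the protocol gives no screening coverage.

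The conclusion rests on the protocol text alone and assumes that no unstated register count was meant to serve as the denominator. It leaves Objectives 1–5, the diagnosed half of the cohort and the Table 3 outcomes among screened patients untouched. Objective 8 is descriptive, so this is a correction that should be made, not a threat to the trial.

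**What to change.** Adopt one rule and carry it through every place that depends on it. Either of two routes is sound.

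**(a) Sample patients eligible for screening.** Take the first 100 consecutive presenting patients per site who are eligible for screening, screened or not, and define that eligibility. Use the presentation date as the enrolment date for this half. Amend the section 8b description and inclusion criterion, section 9c and Table 2. Add the proportion screened to Table 3 and keep prevalence among those screened as a separate outcome. The planned number of patients does not rise, but the sites need a workable list of presenting patients. There will be fewer screened patients and wider prevalence intervals, by a factor of about 1.03 to 2.24 over the assumed coverage range of 95% down to 20%.

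**(b) Keep the screened sample.** Change the Table 4 wording to screened patients. Then either take the proportion screened from a named clinic-level count of presenting patients, for example from the PHC Tick Register, or remove that estimate from section 7 and state in section 3c that prevalence is among patients screened. The edit is smaller and keeps 2,400 screened patients. Its cost is either the extra register count or the loss of the screening step.

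Under either route, the previously diagnosed part of the section 3c prevalence question needs its own count, because section 8b excludes patients with existing disease. If enrolment has begun, record which rule was used at each clinic.

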- What is the effect of Enhanced Adherence Counselling on rates of being alive, in care, and virally suppressed within 3 and 12 months of intervention eligibility?

*Objective 5: Among HIV-infected patients in antiretroviral therapy programs who miss a scheduled appointment by 5 days,* ***evaluate the impact of Early Patient Tracing on retention in care****.*

Research questions:

- What is the effect of Early Patient Tracing on rates of returning to care by 3 and 12 months of tracing?
- What is the effect of Early Patient Tracing on rates of remaining in care by 12 months of tracing?

*Objective 6: For each clinic included in the study,* ***evaluate the overall impact of the Adherence Guidelines on patient outcomes****.*

Research questions:

- What is the effect of the package of interventions on patient retention in care overall?
- What is the proportion of population in need expected to benefit from the package of interventions?

*Objective 7:* ***Estimate the incremental and total cost of each of the interventions*** *listed above compared to standard of care.*

Research questions:

- What is the average cost per patient reached with the intervention?
- What is the average cost per successful outcome achieved?

*Objective 8:* ***Describe the current status of the cascade of care and adherence to treatment for tuberculosis, hypertension, and diabete****s, for the purpose of tailoring the minimum package of interventions to these conditions in the national rollout.*

Research questions:

- What is the prevalence of previously and newly diagnosed TB, hypertension, and diabetes among the population of patients presenting for care at primary health clinics, stratified by age, sex, and HIV status where possible?
- What proportion of diagnosed cases of these conditions are initiated on guideline-compliant treatment?
- What proportion of cases have satisfactory outcomes, based on current guidelines 12 months after diagnosis?
- For each condition, what proportion of patients are lost to care or discontinue treatment during the first 12 months after diagnosis?

Note that the impacts being assessed under Objectives 1-6 are the impacts of the interventions as implemented in the early phase of the national rollout of the guidelines. As is the case with program evaluations in general, results will reflect both intervention efficacy and implementation quality, which may in turn reflect the early learning stage of national policy implementation.

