For all outcomes under Objectives 1-5 and 8, retention in care will be defined as (1-% attrition), with attrition calculated as the sum of reported deaths, loss to follow up, and reported transfers to other facilities. Retention will thus be interpreted as “retained in care at facility,” since the outcomes of patients who transfer will not be known. Where national identification numbers are available, the national death registry will be searched to locate unreported deaths. Loss to follow up will be defined as failure to attend the clinic within 90 days of a scheduled appointment, as stated in the Adherence Guidelines (Table 7 page 49).

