## **f. Data Analysis Objective 8**

For Objective 8, we will describe retention in each stage of TB, hypertension, or diabetes care over time using simple proportions for each stage in the care cascade, stratified as data allow by clinic, province, sex, age group, and HIV status. Estimates will be presented alongside their corresponding 95% confidence intervals to allow evaluation of whether adequate precision was achieved. We will describe time to events (primary outcome, loss to care) using Kaplan-Meier curves. Finally we will look for predictors of poor retention for each condition using logistic regression and Cox proportional hazards regression.

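### Objective 8 contradicts itself on who is sampled and what counts as lost: existing cases are excluded from a prevalence question, treatment is made a condition of sampling in one place only, and loss to follow-up has two definitions

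*Protocol*

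**What the plan says.** **Prevalence.** Among the Objective 8 questions in Section 3.c is: "What is the prevalence of previously and newly diagnosed TB, hypertension, and diabetes among the population of patients presenting for care". The TBHD exclusion criterion in Section 8.b removes "Patients with existing TB, hypertension (diagnosed more than 1 month ago) or diabetes (diagnosed more than 6 months ago". In Table 3 the matching secondary outcome is prevalence among patients screened.

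**Sampling of diagnosed patients.** Section 8.b states: "This TBHD cohort will be made up of patients who have been screened for TBHD (50%) and patients who are newly diagnosed". It sets no treatment condition there or in the TBHD inclusion criterion. Table 4 describes the same half as "100 patients who are recently diagnosed and treated for TB, hypertension and/or diabetes". Section 3.c then asks: "What proportion of diagnosed cases of these conditions are initiated on guideline-compliant treatment", and Table 3 lists a secondary outcome with diagnosed patients as its denominator.

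**Loss to follow-up.** The Objective 8 row of Table 3 says: "Loss to follow up will be defined as being 30 days late for a scheduled appointment". The paragraph after Table 3 opens by stating that it covers Objectives 1-5 and 8, makes loss to follow-up one component of attrition, and ends: "Loss to follow up will be defined as failure to attend the clinic within 90 days of a scheduled appointment".

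**Precision.** Section 10.f plans simple proportions by cascade stage, stratified by clinic and other factors where data allow, with Kaplan-Meier curves and logistic and Cox regression. It adds: "Estimates will be presented alongside their corresponding 95% confidence intervals to allow evaluation of whether adequate precision was achieved".

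**The concern.** Section 7 says Objective 8 exists to find where patients drop out of TB, hypertension and diabetes care, so that the package can be tailored to those conditions. The TBHD cohort is 4,800 of the 8,256 patients in the Summary (58%).

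If existing cases are excluded, a figure reported as prevalence omits most of the disease burden the question asks about. If only treated patients are sampled, the drop-out between diagnosis and treatment disappears from the data. If two loss definitions stand, the 12-month retention figure depends on the analyst's choice.

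The first two cannot be repaired in analysis, because patients who were never abstracted cannot be recovered.

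**Working it through.** **Stated size.** Table 4 takes up to 100 patients for screening and 100 diagnosed patients at each of 24 clinics: 24 × (100 + 100) = 4,800, as stated. Each half is 24 × 100 = 2,400.

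**1. Prevalence.** The question concerns previously and newly diagnosed disease among all presenting patients. The exclusion removes TB and hypertension diagnosed more than 1 month ago and diabetes diagnosed more than 6 months ago. Diabetes diagnosed within 6 months stays eligible, so the excluded group is long-standing disease, not every earlier diagnosis. The cohort can still give the yield of new diagnoses among screened patients without an existing diagnosis. No other Objective 8 source supplies existing cases: the aggregate clinic counts in Section 9.a serve Objective 6 and count patients eligible for the HIV interventions.

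**2. Treatment initiation.** Suppose the Table 4 wording is applied. All 2,400 patients in the diagnosed half have then started some treatment. Let q be the true initiation proportion and d the number of cases found in the screened half. The pooled estimate is

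(2,400 + q·d) / (2,400 + d).

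The protocol gives neither q nor the yield, so both are assumptions:

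| Yield in screened half | d | q = 60% | q = 80% |
|---|---|---|---|
| 5% | 120 | 2,472 / 2,520 = 98.1% | 2,496 / 2,520 = 99.0% |
| 10% | 240 | 2,544 / 2,640 = 96.4% | 2,592 / 2,640 = 98.2% |
| 20% | 480 | 2,688 / 2,880 = 93.3% | 2,784 / 2,880 = 96.7% |

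A true 60% and a true 80% become almost indistinguishable. The same selection reaches the Objective 8 primary outcomes, whose denominator in Table 3 is patients eligible for treatment: diagnosed patients who never started would be missing from it. Under the Section 8.b wording none of this arises.

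**3. Loss to follow-up.** A patient who returns between 31 and 90 days after a scheduled appointment is lost under the Table 3 row and not lost under the paragraph after it. The choice affects retention at 12 months (Table 3), the question on loss during the first 12 months (Section 3.c) and the Kaplan-Meier time to loss (Section 10.f). The protocol gives no distribution of lateness, so the effect cannot be sized.

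**4. Clustering.** Section 10.c says the analysis must account for clustering, but under Objectives 1-5 only. Section 10.f has no equivalent sentence and gives no variance method. Since Table 4 targets no specific sample size for Objective 8, the confidence intervals are its only check on precision. The coefficient of variation in Section 10.b is stated for Objectives 1-5, so the protocol offers no basis for sizing a design effect here.

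**The case against.** The strongest reply is that Objective 8 is descriptive, has no randomised comparison, and lists prevalence, initiation and 12-month retention as secondary outcomes, which Section 10.a makes dependent on data availability. The definitions of its primary outcomes (visit compliance and six-month disease control) contain no contradiction, and Objectives 1-5 are untouched. All of that stands and limits the seriousness. It does not settle which sampling rule or loss definition applies.

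On prevalence, Table 3 already uses the narrower population of screened patients, so the fault lies mainly in the wording of the question. That is accepted, and it points to the simplest remedy.

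On loss to follow-up, the row-specific 30-day rule could be read as overriding a general one. But the general paragraph names Objective 8, so that reading is not secure.

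Two stronger readings are tempting and are not supported:

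- A reader might infer that treatment uptake is fixed at 100% by design. That holds only under the Table 4 wording, only in the diagnosed half, and only for treatment of any kind. The eligibility text in Section 8.b carries no such condition, cases from the screened half also count, and being treated does not make treatment guideline-compliant.
- A reader might infer that the Objective 8 intervals ignore clinic clustering. Section 10.f is silent on the variance method, provides for stratification by clinic, and may leave the method to the SAP. Silence is not a statement that clustering will be ignored.

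**Conclusion.** Three contradictions hold on the protocol's own text and need correction before records are abstracted.

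- The cohort cannot answer the existing-disease part of the prevalence question. This follows from the exclusion alone.
- The two descriptions of the diagnosed half conflict. If Table 4 governs, initiation of any treatment is heavily overstated: a true 60% reads as 93% to 98%, and a true 80% as 97% to 99%, assuming a 5% to 20% yield in the screened half and pooling of the two halves. If Section 8.b governs, there is no such bias.
- Loss to follow-up has two incompatible definitions for the same objective. The direction is clear (the 30-day rule counts at least as many patients as lost), but the size is unknown.

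The handling of clustering in Section 10.f is a clarification only. The effect of the whole point is confined to the descriptive Objective 8 results.

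**What to change.** 1. **Section 3.c:** restate the prevalence question as the yield of new diagnoses among screened patients without an existing diagnosis, in line with Section 8.b and Table 3. This costs only wording. If existing-disease prevalence is still wanted, also count patients excluded for an existing diagnosis, without following them. That may need a wider record review than Section 9.d describes, which selects only newly eligible patients, so feasibility should be checked first.
2. **Table 4:** delete *and treated*, and sample all newly diagnosed patients as in Section 8.b. This costs only wording, but it must be settled before abstraction.
3. **Section 10.a:** reconcile the Objective 8 row of Table 3 with the paragraph after it, so that one loss-to-follow-up definition governs the Objective 8 analysis. The choice is for the investigators; no new data are needed.
4. **Section 10.f (clarification):** state that Objective 8 intervals and regression models will be clinic-clustered. This costs one sentence and a standard software option; intervals will generally be wider where clinics differ.
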